## ***Basic plan of analysis***

Analysis will first be performed to evaluate the comparability of the intervention groups and the control group at study entry in terms of sociodemographic and clinical characteristics. Student's t-test or appropriate non-parametric statistics will be used, depending on the level of measurement. If the groups are found not to be comparable on one or more background variables, those variables will be employed routinely as covariates in subsequent analyses using multivariate models, such as logistic regression.

The proportion of the outcomes in each intervention arm, i.e. consent rates and patients' satisfaction with and preference for a consent procedure, the proportion of patients aware of storage of tissue and research use, and the satisfaction with and preference for a consent procedure of the medical staff, will be evaluated by comparison of the informed consent

versus the opt-out plus group, and the opt-out plus versus the opt-out group by non-parametric or parametric tests as appropriate. Patient characteristics, satisfaction with and preferences for the information and consent procedures will be evaluated according to patient characteristics such as age, educational level, sex, hospital type, type of clinical procedure, and disease type. All analyses will be performed using SPSS.

A qualitative analysis of the information needs and appreciation of the patients for the consent procedures will be evaluated through questions in the questionnaire and telephone interviews with a representative group of patients who completed the questionnaire.

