## ***Patients and methods***

### **Study sample**

The study sample will be composed of 1800 patients, evenly distributed over the three study arms. Sample size is based on an expected response rate (for the questionnaire) of 75%. We will include patients who undergo surgery or biopsy (1600 patients) or blood drawing (200 patients). The former category of patients will contain patients who have a skin condition, a colorectal condition or a condition in the head/neck area. We include patients with malignant and non-malignant conditions of the same tissues or organs with a ratio of about 3:2, dependent on availability in each hospital. The absolute number of patients with specific conditions will also depend on the availability of these patients in the four hospitals. In the VUmc we will not include patients with (malignant and benign) colorectal conditions and malignant head/neck conditions, because almost all of them will also be asked to participate in a biobank (String of Pearls Initiative), which might confuse patients about what they are asked to give consent for. In the NKI-AVL, only patients with malignant conditions will be included. Figure 1 gives an overview of the number of patients in each of the groups in the four hospitals.

We will include patients between the ages of 18 and 80 years. There are two reasons for the upper age limit. First, we have learned from experience that patients over 80 are much less likely to be able or willing to complete questionnaires. Second, and more importantly, the two community hospitals in our study treat more patients over 80 than the two academic hospitals. Including these patients would mean that it would be difficult to determine whether any differences observed between patients from these different types of hospitals should be attributed to age differences or other causes.

Patients should be able to speak and read Dutch and have a sufficient mental capacity to complete the questionnaires by themselves. Patients will be included in the study by their treating physician or nurse practitioner.

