### **Study design including study arms**

In this multicentre randomized controlled trial, 1800 patients will be recruited from academic and community hospitals during an 18 month period (Figure 2). The consent procedures will be offered a short time before or after the tissue or blood is removed, dependent on what is the best timing according to the clinician or nurse practitioner. Patients to be included are

distributed over four hospitals: two academic hospitals and two regional hospitals: the NKI-AVL, the Vrije Universiteit Medical Center (VUmc), the Spaarne hospital in Hoofddorp and the Kennemer hospital in Haarlem. Inclusion of academic and community hospitals will increase the external validity (i.e. generalizability) of the study results.

Patients will be randomized, stratified by hospital and diagnosis, to opt-out plus, informed consent or opt-out (control group) in collaboration with [name] (statistician NKI-AVL). Clinicians and nurse practitioners who will carry out the intervention will receive envelopes that each contain the paperwork (checklist, brochure in opt-out plus and informed consent arms and return envelopes) for one patient. The envelopes will be put in order of the randomization. Clinicians and nurse practitioners will write down his or her name, the patient's name, patient number, diagnosis, date and method of tissue removal on the checklist. A random selection of diagnoses on the checklists will be compared with the diagnoses in the medical files to check their validity. If the validity is found to be poor, all diagnoses will be checked.

In our previous intervention study (see preliminary results) we asked patients informed consent before the start of the intervention. However, patients felt that it was confusing to be asked informed consent for a study in which they were asked to provide informed consent. To prevent this kind of confusion in the current study, we will not ask consent for the randomization and the intervention. We believe that not asking consent for the randomization is suitable to our study because the informed consent procedure bears no potential harm to the participants, the intervention is of importance for future clinical research, the intervention includes no invasive procedure for the participants, and at least the standard care is offered to participants in the control group.

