### ***Sample size, statistical power***

Sample size is based on an expected response of 75%, allowing sufficient power to address the major outcomes, i.e. consent rates and preferences for procedures, in different subgroups of e.g. hospitals, age and gender. In order to test the hypothesis that the two interventions result in a difference of at least 10% in consent rates, 0.1% non-consent in the opt-out plus or opt-out group versus 10% in the informed consent group, 121 patients per group are needed (80% power and a 2-sided alpha of 0.05; with continuity correction). The difference of 10% is based on our earlier research and the difference is considered a relevant loss of patient materials for research which may lead to selection bias. Because the setting of diagnosis and treatment is different between surgical and outpatient settings and also between general and academic hospitals, it is important to be able to compare the responses in these subgroups. We have also shown in our earlier studies that educational level is associated with preference for a certain procedure and this may also drive response rates of patients. Therefore we propose to include in each intervention group up to 600 patients to be able to conduct subgroup analysis and include adjustment factors; with a response rate of 75% and hence with 450 participants per group we could stratify for 3 to 4 factors, i.e. 90-150 per subgroup, and still have enough power to investigate a difference in response rate of 0.1% versus 10%. Patients will not be stratified by education or sex; we expect these two factors to be equally distributed across groups.

Another reason to obtain a large sample size is that the percentage of non-consenters is small, while it is important to assess their opinions and reasons for non-consent. In the earlier intervention study, 4.6% of respondents indicated in the questionnaire that they wanted to withhold consent or that they did not know whether they wanted to. A sample size of 1800 patients and a response rate of 75% will lead to approximately 62 patients who want to withhold consent or are not sure which choice to make.

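### Covariates are chosen by baseline comparability tests, and the arm comparisons name no term for the randomisation strata (hospital and diagnosis)

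*Protocol*

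**What the plan says.** The protocol's Basic plan of analysis starts by comparing the arms on sociodemographic and clinical characteristics: "Student's t-test or appropriate non-parametric statistics will be used, depending on the level of measurement". It then sets the adjustment rule: "If the groups are found not to be comparable on one or more background variables, those variables will be employed routinely as covariates". These covariates go into multivariate models, with logistic regression given as an example. No threshold and no list of variables is stated.

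The two arm contrasts are informed consent "versus the opt-out plus group, and the opt-out plus versus the opt-out group by non-parametric or parametric tests as appropriate". No stratum term is named. Hospital type and disease type appear in that section only as factors by which results are broken down: satisfaction and preference "will be evaluated according to patient characteristics such as age, educational level, sex, hospital type, type of clinical procedure, and disease type".

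Two other sections bear on the rule. Under Study design including study arms: "Patients will be randomized, stratified by hospital and diagnosis". Under Sample size, statistical power, the protocol reports from its earlier studies that "educational level is associated with preference for a certain procedure", adds that education may also affect response, and says that patients will not be stratified by it. The same section uses unnamed adjustment factors as one reason for the large sample.

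**The concern.** In a randomised trial, a baseline test mostly detects chance differences. A rule that adjusts only for what such a test flags leaves the final model to be settled after the data are seen. It also selects on the wrong property, since a covariate is worth including because it predicts the outcome, not because it happens to differ between arms.

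Here the rule works against the design. Stratified randomisation makes hospital and diagnosis nearly equal across arms, so a search for imbalance will tend to pass them over. If they predict the outcome, an analysis that ignores them uses a standard error that is too large, and the benefit of stratifying is lost. Education, the one predictor of preference that the protocol names, is left to the same chance. The preference comparison is planned at only 75% power, so avoidable loss is worth removing.

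**Working it through.** No stated figure is in dispute. The protocol's own preference calculation supplies the setting for the check.

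**1. The plan's figure.** Inputs: 43% versus 34%, 450 per arm, 75% power, two-sided, continuity correction (Sample size, statistical power). The alpha level is not given at that point; 0.05 is assumed.

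- Without correction: n = [1.96·√(2·0.385·0.615) + 0.6745·√(0.43·0.57 + 0.34·0.66)]² / 0.09² = 405 per arm.
- With correction: (405/4)·[1 + √(1 + 4/(405·0.09))]² = 427 per arm.
- Power at 450 per arm is about 77% with correction and 79% without, so the statement that 450 suffices holds.

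**2. Chance selection.** With k independent background variables, each tested once at an assumed 5%, P(at least one flagged) = 1 − 0.95^k. For k = 5, 8 and 12 this gives 23%, 34% and 46%. The protocol gives neither k nor the 5%.

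**3. Error rate after selection.** A simulation used 450 per arm, two arms, 8 covariates of which 2 were prognostic, and 10,000 runs. At least one covariate was selected in 33-34% of trials. Type I error after selection was 4.95% with moderately prognostic covariates and 4.1% with strong ones, against about 5.1% for a set fixed in advance. The distortion is downward.

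**4. Ignoring the strata.** With allocation balanced within strata, the true variance of the difference in proportions uses the average of p_s(1 − p_s). The unstratified test uses p̄(1 − p̄), which is larger. To first order, with a between-stratum SD of τ on the logit scale, the ratio of nominal to true standard error is 1/√(1 − p̄(1 − p̄)τ²). At p̄ = 0.34:

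- τ = 0.3: 1/√(1 − 0.2244·0.09) = 1.010
- τ = 0.5: 1/√(1 − 0.2244·0.25) = 1.029

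The approximation weakens for larger τ, so a simulation covers the range: 450 per arm, 12 equal strata, exact balance within strata, 20,000 runs, preference 34% under the null and 34% versus 43% under the alternative. It compares the unstratified z-test with the Cochran-Mantel-Haenszel (CMH) test. The τ values and the 12 strata are assumptions.

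| τ (assumed) | Stratum preference, mean 34% | Nominal/true SE, null; alternative | Type I, unstratified | Type I, CMH | Power, unstratified | Power, CMH | Gain (points) |
|---|---|---|---|---|---|---|---|
| 0 | 34% | 1.00; 1.01 | 5.1% | 5.1% | 79.8% | 79.8% | 0.0 |
| 0.3 | 23-47% | 1.01; 1.01 | 4.9% | 5.1% | 79.8% | 80.0% | 0.2 |
| 0.5 | 17-55% | 1.02; 1.04 | 4.5% | 5.0% | 80.5% | 82.0% | 1.5 |
| 0.8 | 10-67% | 1.06; 1.08 | 3.7% | 5.1% | 81.2% | 84.4% | 3.2 |
| 1.2 | 5-79% | 1.13; 1.14 | 2.7% | 5.3% | 82.7% | 88.4% | 5.7 |

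The simulation error is about 0.15 points on a 5% error rate (√(0.05·0.95/20000)) and 0.3 points on 80% power (√(0.8·0.2/20000)). With no strata effect nothing changes.

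**The case against.** The strongest case against is that the harm is small and on the safe side. That is right about direction: both the selection rule and the missing strata push type I error below 5%. A reader might infer a risk of false positive findings, and the calculations do not support it. For weakly prognostic strata the loss is negligible.

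Several stronger readings are also tempting and do not hold:

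- **The strata can never enter, or are left out of the analysis.** Questionnaire outcomes come from an expected 75% of patients, so hospital or diagnosis could be unbalanced among respondents and be selected. Both also figure in the breakdowns. A statistical analysis plan that is not shown could name them. What stands is that the protocol states its own rule, and that rule tends to miss them.
- **The baseline tests cannot handle categorical factors.** The protocol allows non-parametric alternatives according to the level of measurement.
- **Omitting education mis-states the standard error.** Education is not a stratification factor, so omitting it loses precision but leaves the error rate intact.
- **The logistic model will fail for consent because an opt-out arm has no events.** Taking 0.1% non-consent literally, 0.999^600 = 0.549 per arm, so at least one of two such arms has no event with probability 1 − 0.451² = 0.80. But logistic regression is only an example, used if imbalance is found, and the plain comparison leaves room for an exact test. The 0.1% is itself uncertain: the stated 121 per group reproduces at 1% versus 10%, whereas 0.1% versus 10% gives 95. At 1%, 0.99^600 = 0.0024, or about 0.5% for either arm.
- **The comparison of hospital types is confounded by case mix.** Recruitment does differ by site ("In the NKI-AVL, only patients with malignant conditions will be included"), but that is a separate, secondary question that does not touch the randomised contrasts. The figure with the cell counts is not available, so the overlap cannot be judged.

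**Conclusion.** The point stands as a modest, inexpensive correction. The protocol fixes a data-driven covariate rule, names no stratum term in the arm comparisons, and leaves a known predictor of preference to chance. For preference at 450 per arm, ignoring the strata makes the standard error about 1-4% too large if strata effects are modest (τ of 0.3 to 0.5) and up to about 14% if they are strong (τ of 1.2). The power lost runs from about 0.2 to 6 points, and type I error falls to between about 4.9% and 2.7%. These sizes rest on assumed strata effects, 12 equal strata and exact balance. The protocol gives no strata effects, so the range should be read as conditional. The validity of a positive result is not in doubt.

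Non-response strengthens the case for a fixed set: imbalance among respondents need not be pure chance, and a significance test is a poor guide to which imbalance matters.

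**What to change.** - Delete the rule that selects covariates by baseline test. Keep the baseline tables as description.
- For patient questionnaire outcomes (satisfaction, preference, awareness), adjust each arm contrast for hospital and diagnosis, plus education, age and sex, all named in advance. In a logistic model the gain is in power and a correct error rate; the interval for the odds ratio need not become narrower.
- For consent rates among all randomised patients, use a method stratified by hospital and diagnosis only, such as a Mantel-Haenszel risk difference or an exact stratified test. These also cope with very few non-consent events. Education should stay out here: patient characteristics are collected by questionnaire, so it would be missing for the expected 25% who do not respond.
- Leave the medical-staff outcomes outside this change, because patient covariates do not apply to them.

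The cost is a change of wording and slightly more analysis work, with no new data collection. Sparse diagnosis strata may need to be pooled, by a rule set before the outcomes are seen.

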## **Hypotheses**

Hypotheses regarding the primary study outcomes are:

1. Patients' will be significantly more satisfied with the informed consent and opt-out plus consent procedures than with the opt-out consent procedure
2. Most patients will prefer the opt-out plus consent procedure, the lowest proportion of patients will prefer the opt-out consent procedure.
3. Significantly more patients will be aware of storage of tissue and research use in the informed consent and opt-out plus procedures than in the opt-out procedures.
4. Consent rates will be highest in opt-out and opt-out plus.
5. Members of the medical staff will be most satisfied with and prefer the opt-out and opt-out plus procedures.

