## **Outcomes**

The primary study outcomes will be used to determine which consent procedure serves the needs of patients, clinicians and scientific research best. If one of the three consent procedures serves the needs of all three of these parties best, we will conclude that this consent procedure is the best candidate to become the standard procedure in the Netherlands that prescribes whether and how patients should be asked consent for the use of residual tissue. If the needs of these three parties are best served by different consent procedures, or if it is unclear which consent procedure serves the needs of one or more of the parties best, we will organize an invitational conference in which we invite different stakeholders, such as clinicians, patient organizations and researchers, to discuss how to translate our research findings into clinical practice.

Which consent procedure serves a party's needs best will be decided along the following lines:

- For patients: satisfaction with the received information in the 'best procedure' should be significantly higher than in the consent procedure with the lowest satisfaction rates. Further, the consent procedure should have the highest preference rates among respondents, with a minimum of a 10% difference with the consent procedure with the lowest preference rate. Additionally, the proportion of patients aware of storage of tissue and research use should be at least as high as in the other two groups.

- For clinicians: satisfaction with the received information in the ‘best procedure’ should be significantly higher than in the consent procedure with the lowest satisfaction rates. Further, the consent procedure should have the highest preference rates among participating clinicians and nurse practitioners, with a minimum of a 10% difference with the consent procedure with the lowest preference rate. Additionally, more than 75% of the responding medical staff should indicate that the consent procedure ‘never’ or ‘seldom’ interferes with giving clinical information.
- For research: consent rates for the procedure for which patients and/or clinicians have the highest preference should be at least as high as consent rates in the two other procedures.

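### The analysis section lists two of the three pairwise contrasts and omits informed consent versus opt-out, which hypotheses 1 and 3, the sample size section and possibly the decision rule require

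*Protocol*

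**What the plan says.** For the primary outcomes (consent rates, patient satisfaction and preference, awareness, staff satisfaction and preference), the Basic plan of analysis sets the informed consent arm "versus the opt-out plus group, and the opt-out plus versus the opt-out group by non-parametric or parametric tests as appropriate". That makes two contrasts: informed consent versus opt-out plus, and opt-out plus versus opt-out.

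Other sections of the Protocol call for the third pair, or may do so:

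- Hypothesis 1: patients will be "significantly more satisfied with the informed consent and opt-out plus consent procedures than with the opt-out consent procedure".
- Hypothesis 3 claims that a significantly larger share will be found "aware of storage of tissue and research use in the informed consent and opt-out plus procedures than in the opt-out procedures".
- Hypothesis 4: "Consent rates will be highest in opt-out and opt-out plus".
- Outcomes, for patients and again for clinicians: satisfaction in the best procedure "should be significantly higher than in the consent procedure with the lowest satisfaction rates".
- Outcomes, for research: consent rates for the preferred procedure "should be at least as high as consent rates in the two other procedures".
- Sample size, statistical power: the calculation sets 0.1% non-consent in either opt-out plus or opt-out against 10% in informed consent.

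Study objectives says in general terms that all three procedures will be compared on the primary outcomes. It names no contrasts.

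**The concern.** The analysis section does not leave the contrasts open. It lists them, and the list is one pair short of what the hypotheses claim. An analyst who follows it exactly would test opt-out plus against opt-out for hypotheses 1 and 3, but would have no listed test for the other half of each, informed consent against opt-out.

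The omitted pair may also be the deciding one. Hypothesis 1 expects opt-out to be lowest on satisfaction. The sample size section reports satisfaction in previous research of 82% under informed consent and 65% under opt-out plus. If both patterns recur, best versus lowest is informed consent versus opt-out. The outcome of that rule feeds the choice of a candidate national procedure.

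**Working it through.** **1. Contrasts needed against contrasts listed** (IC = informed consent, OO+ = opt-out plus, OO = opt-out).

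| Source in the Protocol | Pairs implied | Pair not on the list |
|---|---|---|
| Hypothesis 1, satisfaction | IC > OO, OO+ > OO, both significantly | IC vs OO |
| Hypothesis 3, awareness | IC > OO, OO+ > OO, both significantly | IC vs OO |
| Hypothesis 4, consent rates | OO > IC, OO+ > IC; no mention of significance | IC vs OO |
| Sample size, consent rates | OO+ or OO vs IC | IC vs OO |
| Outcomes, satisfaction rule | best vs lowest, significantly | IC vs OO, if these are the extremes |
| Outcomes, research rule | preferred procedure vs both others; no test named | IC vs OO, if IC or OO is preferred |

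**2. The protocol's own sample size.** Stated: 121 per group for 0.1% vs 10%, 80% power, two-sided 0.05, continuity correction.

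- n = [1.96·√(2·0.0505·0.9495) + 0.8416·√(0.001·0.999 + 0.10·0.90)]² / 0.099² = (0.607 + 0.254)² / 0.0098 ≈ 75.6, so 76.
- With the correction, (n/4)·[1 + √(1 + 4/(n·0.099))]² ≈ 94.7, so 95.

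The printed inputs therefore give 95, not 121. The value 121 comes out at 90% power. The difference is on the safe side and the point here does not depend on it. For this contrast, power with the correction is above 99.9% at 450 or 600 per arm.

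**3. Can the two listed tests stand in for the third?** The documents give no opt-out satisfaction rate, so the following is an assumption: IC 82%, OO+ 77%, OO 72%, with 450 per arm (75% of 600).

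- z = d / SE0, where SE0 = √(2·p̄(1−p̄)/450).
- Power = Φ[(d − 1.96·SE0)/SE1], where SE1 = √{[p1(1−p1) + p2(1−p2)]/450}.

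| Pair | d | SE0 | SE1 | z | p if observed exactly | Power |
|---|---|---|---|---|---|---|
| IC vs OO+ (listed) | 0.05 | 0.0269 | 0.0269 | 1.86 | 0.063 | 46% |
| OO+ vs OO (listed) | 0.05 | 0.0291 | 0.0290 | 1.72 | 0.085 | 41% |
| IC vs OO (omitted) | 0.10 | 0.0281 | 0.0279 | 3.56 | 0.0004 | 95% |

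Subtracting the continuity term 1/450 from d in the power formula gives about 43%, 38% and 94%, so the picture is the same. Both listed tests can miss while the omitted one is clear. Significance of the adjacent pairs neither implies nor excludes significance of the outer pair.

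**4. Range for the omitted contrast.** With IC at 82% and 450 per arm, power is about 95% if opt-out is 72% and above 99.9% (with the correction) if opt-out is 65%. The 65% is the previous opt-out plus rate, borrowed here for opt-out.

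**5. Multiplicity.** With each test at 0.05, the chance of at least one false positive within one outcome is at most 2 × 0.05 = 10% for the two listed contrasts and at most 3 × 0.05 = 15% for all three. Were the tests independent, these would be 1 − 0.95² = 9.8% and 1 − 0.95³ = 14.3%.

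**The case against.** A reader might infer from the gap that the contrast is never made, that any such test would be post hoc, or that the decision rule could not be applied. The documents do not support these readings.

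- The sample size section names and sizes opt-out against informed consent for consent rates, and Study objectives promises a three-way comparison. The section at fault is headed as a basic plan. A statistical analysis plan, not available for this review, may name the pair. The fair statement is that the protocol's list does not specify it.
- Hypotheses 1 and 3 state the comparison in advance, with direction and with a claim of significance. The Outcomes section states the best-versus-lowest test in advance. Running it would carry out what is written elsewhere in the protocol.
- The satisfaction rule can still be applied by running the test that it prescribes. The pair is missing only when informed consent and opt-out are the extremes. Opt-out plus may come out highest instead: the sample size section expects it to beat informed consent on satisfaction, although the figures printed there point the other way. Best versus lowest could then be opt-out plus against opt-out, which is listed.

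Hypothesis 4 and the research rule are also weaker support, because neither mentions significance or names a test. No estimate is biased, and allocation, data collection and sample size are untouched.

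What remains is that this is not detail left for later. A stated list conflicts with the protocol's own hypotheses, and a general objective that names no contrasts does not resolve the conflict.

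**Conclusion.** The point holds as an internal inconsistency. The analysis section lists two of three pairwise contrasts. The third is explicit in hypotheses 1 and 3, is used in the consent-rate sample size, is implied by hypothesis 4, and is needed for the satisfaction rule when informed consent and opt-out are the extremes.

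Its size depends on the true satisfaction rates. In the assumed 82/77/72% case the listed tests have roughly even odds or worse of detecting their differences, while the omitted test would almost certainly detect its own. That pattern is an illustration. Whether the trial is exposed to it depends on an opt-out rate that the protocol does not give. The part of hypotheses 1 and 3 left without a listed test does not depend on any assumed rate.

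**What to change.** Add informed consent versus opt-out to the comparisons in the Basic plan of analysis for patient satisfaction, awareness and consent rates, so that the list agrees with the Hypotheses, Outcomes and Sample size sections.

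Cover the same pair for staff satisfaction, because the best-versus-lowest rule applies to clinicians too. The post-intervention questionnaire asks staff about all three procedures, so their ratings are not from independent groups. The method should allow for repeated ratings by the same person.

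Naming the contrast is enough to cure the mismatch. If family-wise control is wanted, an overall three-arm test at 0.05 followed by the three pairwise tests at 0.05 each holds the error for patient outcomes, because there are exactly three groups. It does so within each outcome only. Across satisfaction, awareness and consent, each handled this way, the error could still reach 3 × 0.05 = 15% (14.3% if independent), and the plan should say whether that is accepted.

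The cost is a sentence or two of text and one extra contrast per outcome. No more patients and no change to data collection are needed.
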